### Recruitment

Participants will be approached and recruited whilst they are inpatients at the Amputee Rehabilitation Unit. Newly admitted potential participants will be identified by clinical staff (JG, CC), approached by the researcher ([name]), initially screened, and provided with oral and written information. Participants who pass initial screening tests and are willing to participate will have a final eligibility check by [name] before enrolment in the study (Figure 1). Signed, informed consent will be obtained from all participants before enrolling them in the study. Those declining to participate will be asked briefly for their reasons. As the study is a feasibility study, no sample size calculation has been performed [21]. An arbitrary number of 20 participants was deemed adequate to provide information on recruitment, randomization and acceptability of acupuncture and answer the objectives of this trial [23].

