### Randomization, allocation concealment and blinding

Randomization and allocation concealment will be used to ensure against selection bias [29]. Prior to commencement of the study, a researcher (NR) not involved in the day-to-day execution of the study will randomly allocate and conceal allocation. A copy of the randomized sequence will be kept in a locked cabinet and not shared with study personnel. The researcher ([name]) who will enrol participants and assign them to either acupuncture intervention or control will not know the random sequence or treatment allocation.

Randomization will be achieved using a computer-generated random numbers table and will be unstratified and balanced (1:1). Permuted blocking will be used to achieve balance between study arms. A block size of four will be used in this study. Allocation concealment will be implemented using sequentially numbered, opaque sealed envelopes. The envelopes will be opened sequentially only after participant’s details are written on each envelope.

Participants and practitioners involved in the study will not be blinded. However, the researcher collecting outcome measures ([name]) will be blind to the participant’s allocation.

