### Outcome measures

Recommendations from the Assessment Committee of the Neuropathic Pain Special Interest Group [30] and the Initiative on Methods, Measurements, and Pain Assessment in Clinical Trials [31] were taken into consideration when developing outcome measures for use in this trial.

The primary outcome measure will be an 11-point numerical rating scale to record pain intensity. Pain will be rated by a number describing average pain over the previous week, using the anchors 0, meaning ‘no pain’, and 10, meaning ‘pain as bad as you can imagine’ [31]. The numerical rating scale is an appropriate measure of pain intensity [32] and is a recommended outcome measure for clinical trials of chronic pain treatment effectiveness [31].

Secondary outcome measures will include a numerical rating scale measuring ‘worst’ pain, the short-form McGill Pain Questionnaire 2 (SF-MPQ-2), EQ-5D-5 L, Hospital Anxiety and Depression Scale, 10-Item Perceived Stress Scale, Insomnia Severity Index, and Patient Global Impression of Change.

The McGill Pain Questionnaire and its short form (SF-MPQ) are generic questionnaires (applicable to any pain), whose reliability and validity have been extensively documented [33]. The SF-MPQ-2 is a 22-item questionnaire that uses a 10 point rating scale and records the major symptoms of both neuropathic and non-neuropathic pain [34]. It is reliable and valid for measuring diverse chronic pain [35].

The EQ-5D measures health-related quality of life and although not validated for use in neuropathic trials, results appear robust in neuropathic trials with a large sample size or when recording a large-pain relief response in the active group [30]. The EQ-5D-5 L has the same core dimensions as the EQ-5D but instead of a three-point rating scale it uses five levels.

The Hospital Anxiety and Depression Scale measures emotional function and is responsive to change in neuropathic pain clinical trials [30]. It includes seven depression and seven anxiety items to cover cognitive and emotional aspects of depression and anxiety and is reliable and valid for assessing emotional distress in a medical population [36].

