### Analysis

As this is a feasibility study, emphasis will be on feasibility and not on statistical significance of results [21]. Compliance with the protocol will be examined through number counts on drop outs or numbers of missed treatments, completion rates of outcome measures, and their perceived appropriateness and deviation from the protocol. Data will be collected on the use of rescue medication and adverse events (captured through open-ended prompts by practitioners at each intervention time point). Details of any participants who are excluded from the study will be reported and exclusion will be distinguished from attrition.

All statistical analysis will be undertaken using SPSS Version 21 software. The analysis will test for within-patient and between-group differences in measurements taken at the beginning of the study, during the study, at the end of the study and one month after completion of the study. An intention-to-treat approach will be taken [44]. To include missing data, any missing data will be imputed using the last observation carried forward [45].

The null hypothesis is that there is no difference in change in the primary outcome measure between group A and C at the end of intervention (end of week 4). Statistical analysis will be performed to verify rejection of the null hypothesis with a *P* = 0.05 taken as indicative of statistical significance. Nonparametric tests will be used in inferential analysis. The nonparametric Mann–Whitney *U* test will be used for analysis between groups. The difference between baseline and last observation scores will be analyzed using Wilcoxon signed-rank test. The effect size (Cohen’s *d*) will be calculated to provide information on the relative magnitude of difference [46]. All secondary outcome measures will be treated in the same way as the primary outcome. Categorical and continuous baseline characteristics will also be analyzed to test for between-group differences.

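### The arm comparison ignores baseline pain except by subtraction, and the within-patient and baseline tests add nothing on treatment: a minor inefficiency, not a bias

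*Protocol article*

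**What the plan says.** All of this is in the Protocol article, Analysis, unless another section is named.

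- **Hypothesis:** "The null hypothesis is that there is no difference in change in the primary outcome measure between group A and C" at the end of week 4. The outcome, under Outcome measures: "The primary outcome measure will be an 11-point numerical rating scale to record pain intensity", rated as the past week's average.
- **Tests:** "Nonparametric tests will be used in inferential analysis". Mann–Whitney is assigned to the comparison of arms. No covariate is named.
- **Within patients:** "The difference between baseline and last observation scores will be analyzed using Wilcoxon signed-rank test".
- **Baseline:** "Categorical and continuous baseline characteristics will also be analyzed to test for between-group differences".
- **Estimate:** Cohen's d. The text does not say whether it is computed on change or on week-4 scores, and mentions no adjustment. Objective 7 (Background) and the Abstract's discussion carry the effect size into a future sample size calculation.
- **Size:** "As the study is a feasibility study, no sample size calculation has been performed" and "An arbitrary number of 20 participants was deemed adequate to provide information on recruitment, randomization and acceptability of acupuncture" (Recruitment). With 1:1 allocation that is about 10 per arm.
- **Limits on interpretation:** Analysis puts feasibility ahead of significance. Discussion says the tests serve to try out the procedure and will not be read as showing whether acupuncture works.

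That Mann–Whitney is applied to change follows from the hypothesis and the named test together; no single sentence says so. Whether the Wilcoxon test is run by arm or pooled is not stated.

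**The concern.** Under Assessment, every participant gives a pain score at enrolment. Subtracting it from the week-4 score fixes the baseline coefficient at 1, whatever the data say. When the two scores correlate only moderately, this over-corrects a chance baseline difference and adds noise. ANCOVA estimates the coefficient from the same data.

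This deserves a note even in a feasibility trial, because the tests are there to rehearse the later procedure and the effect size is meant to be reused. A rank-test P value cannot be reused for planning. A d on change can be reused only by someone who also knows the correlation behind it.

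The other two sets of tests raise a separate issue. A baseline-to-last-observation test compares no arms. With the last observation carried forward, that observation may also fall in different weeks for different people. Significance tests of baseline variables after concealed randomization test a null hypothesis that holds by design.

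**Working it through.** The protocol gives no power, SD or effect size, so there is no figure to reproduce. From the protocol: 10 per arm, a 0–10 integer scale, entry at 5 or more, alpha 0.05 (two-sided assumed). Assumed: baseline/week-4 correlation r of 0.3 to 0.7 and, for the simulations, an unselected mean of 5.5 and SD of 2.

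**1. Precision by formula, no truncation.** With equal variances s² at both times, the per-person variances are:

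- change score: 2(1−r)s²
- ANCOVA: (1−r²)s² × 17/16, where 17/16 = 1 + 1/(20−4) is the cost of estimating one slope.

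SE ratio (change/ANCOVA):

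- r = 0.3: √(1.4 / (0.91 × 1.0625)) = 1.20
- r = 0.5: √(1.0 / (0.75 × 1.0625)) = 1.12
- r = 0.7: √(0.6 / (0.51 × 1.0625)) = 1.05

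**2. Precision with the entry rule, simulated (6,000 to 8,000 trials per setting).** Two extremes were used: the screening rating is the baseline score itself, or it is a separate item exchangeable with the baseline and week-4 scores.

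| Unselected r | SE ratio, same score | SE ratio, separate item | Power for 2 points, same score: Mann–Whitney v ANCOVA |
|---|---|---|---|
| 0.3 | 1.07–1.09 | 1.22–1.23 | 46% v 56% |
| 0.5 | 1.04–1.05 | 1.15–1.17 | 56% v 64% |
| 0.7 | 1.01 | 1.08–1.09 | 76% v 79% |

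Selection and rounding lower the correlation that remains in the trial. If only 0.1 remained, the formula gives √(1.8 / (0.99 × 1.0625)) = 1.31. Roughly 30% is therefore an outer value. Type I error of Mann–Whitney on change was 4% to 5% throughout. Part of the power gap is the discreteness of the rank test at 10 per arm.

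**3. Against sampling error.** For an observed d of 0.5, SE = √(20/100 + 0.25/40) = 0.454, so the 95% CI is 0.5 ± 0.89, or −0.39 to 1.39. Dividing the half-width by 1.09 leaves about 0.82; dividing by 1.3 still leaves about 0.68.

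**4. Reuse of d.** Take one raw effect of 0.5 week-4 SD. On the change scale d = 0.5/√(2(1−r)), which is 0.42, 0.50 and 0.65 for r = 0.3, 0.5 and 0.7. With 80% power and two-sided 5%, n per arm = 2(1.96 + 0.84)²/d² ≈ 15.7/d². That is 15.7 × 1.4/0.25 ≈ 88 at r = 0.3 and 15.7 × 0.6/0.25 ≈ 38 at r = 0.7. The raw effect is the same in both; only r differs.

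**5. Wilcoxon with no treatment effect and no true change.**

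- Screening score is the baseline score: mean pain falls 0.73, 0.53 and 0.33 points for r = 0.3, 0.5 and 0.7, and the test rejects within an arm in about 15%, 12% and 8–9% of trials. If run by arm, exactly one arm is significant in about 27%, 21% and 15%.
- Exchangeable separate item: no mean drop, and rejection about 5%.

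**6. Baseline tests.** The number of variables is not given. For k independent tests, P(at least one P < 0.05) = 1 − 0.95^k: 23% for 5, 40% for 10, 54% for 15.

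**The case against.** The best defence is that nothing in the trial turns on this. The rank test holds its level and is a reasonable choice for a bounded integer scale with 10 per arm. Twenty participants is an admittedly arbitrary number with no efficacy power to lose. None of the listed success criteria uses a P value, and the protocol disclaims any reading about effectiveness. An effect size is planned, and an article may leave its interval to the full plan. All of that stands, and it keeps the point minor. It does not cover the reuse of d for planning, or tests that say nothing about the arms.

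Stronger readings that a reader might infer, and that the protocol does not support:

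- *The variance saving is the textbook (1+r)/2, or 0.65 to 0.85.* That ignores the entry threshold and the cost of the covariate.
- *The entry rule guarantees regression to the mean.* Eligibility uses current pain on a verbal scale, while the outcome is a weekly average on a numerical scale. If those scores are exchangeable with week 4, the drop disappears. The two harms also trade off: the truncation that produces the drop shrinks the gain from ANCOVA.
- *Baseline P values will decide whether randomization worked.* The Abstract lists that as a feasibility question, but no success criterion uses baseline tests.

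**Conclusion.** The point holds as a minor one. The planned comparison of arms is valid but less precise than it need be. The excess SE is about 1% to 9% if the entry rule truncates baseline and up to roughly 30% if screening is a separate rating, for assumed correlations of 0.3 to 0.7. The protocol does not give the correlation, so the size cannot be fixed further, and in either case the sampling error with 20 participants is larger. The more practical defect is that a d on change depends on that same correlation and so transfers poorly to the definitive trial. The Wilcoxon test compares no arms and rejects under no effect between about 5% and about 15% of the time, depending on how closely screening and baseline scores coincide. The baseline tests can flag only chance differences. A reader might infer that the primary test is biased or that the trial's conclusions are at risk. The type I error and the protocol's own limits on interpretation argue against both.

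**What to change.** In Analysis:

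- For week-4 average pain, report the ANCOVA mean difference between arms adjusted for baseline pain, with its 95% CI, the residual SD and the baseline/week-4 correlation. Keep Mann–Whitney on change as a sensitivity analysis.
- Treat secondary scales that have a baseline in the same way. Exempt the Patient Global Impression of Change: Assessment collects it only from the end of week 1, so it has no baseline to adjust for or subtract.
- If Cohen's d is kept, state which scores and which SD it uses.
- Describe baseline characteristics by arm without P values.
- Drop the Wilcoxon tests, or label them descriptive and define the last observation.

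The cost is a rewording of one section. No new data are needed, and the model is standard in the software already named. The downside is a linearity assumption and one degree of freedom with 20 participants; the retained rank test serves as a check.

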### Data management and reporting

The Consolidated Standards of Reporting Trials (CONSORT) [48] and Standards for Reporting Interventions in Clinical Trials of Acupuncture (STRICTA) [49] will be adhered to when reporting. Data will be stored securely with no participant identifiers included. Access to and handling of data will be restricted to those involved in the study. All disseminated findings will contain no participant-identifiable data.

## Discussion

Currently, no genuine placebo-controlled acupuncture trials exist [50]. Different types of sham acupuncture have been implemented in acupuncture trials, including; shallow needling of acupuncture points, using nonpenetrating needles, needling non-acupuncture points and needling acupuncture points that are not indicated for that specific condition, but none of these methods is physiologically inert [50] and sham acupuncture might have some level of effectiveness [51]. Therefore, despite a lack of blinding introducing ascertainment bias, sham acupuncture will not be used in this study and will not be used in a future definitive trial.

Inferential statistical analysis and hypothesis testing will be completed only to pilot procedure and will not be interpreted as a measure of effectiveness of acupuncture. Effectiveness will only be established after completion of a fully powered randomized controlled trail.

Results of this study will be disseminated through publication.

## Trial status

Recruitment commenced in October 2014 and it is anticipated that it will finish by October 2015.

## Abbreviation

SF-MPQ-2: short-form McGill Pain Questionnaire 2
